A recent meta-analysis suggests VRET to be slightly, but significantly, more effective than IVET (in vivo exposure therapy) [27]. Although, VRET provides a powerful means of modifying affect, because of its immersive nature, it has not been tested yet as a therapy for dentally related anxiety or dental phobia. In an effort to answer this question, we will use VRET simulation software for the treatment of dental phobia and test its efficacy in the present study. The primary objective of the present study is to determine the efficacy of VRET versus an informational pamphlet control group in terms of dental trait and state anxiety reductions at 1 week, 3 months and 6 months follow-up among a sample of patients suffering from dental phobia. The secondary objectives are to determine (a) the real-time effect of VRET on the course of participant’s physiological response (HR) on exposure with a series of dentally related cues during therapy and (b) the relation between subjective (i.e., presence) and more objective (i.e., HR) measures during VRET. It is hypothesized that: (a) VRET would result in a significantly reduced level of dental trait anxiety [measured by MDAS (Modified Dental Anxiety Scale) and Dental Fear Survey (DFS)] and state anxiety [indexed by VAS-A (Visual Analogue Scale-Anxiety)] at 1 week, 3 months and 6 months follow-up compared to the informational pamphlet control group, (b) VRET would result in significantly higher reduced physiological arousal (i.e., HR) to dental anxious stimuli/cues relative to the baseline HR values following therapy, (c) VRET will demonstrate a positive correlation between subjective and objective measures of ‘presence’.

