### Procedure

After arrival at the dental office, participants will receive a detailed explanation about the study from the researcher. All participants will be asked for a written informed consent to participate in the study. The participants will be interviewed to screen for dental phobia using the “Phobia checklist” by the researcher. The interview will take 0.5 to 1.5 hours. The participants will undergo the baseline assessments (T0) which will include use of questionnaires to record the participants’ characteristics such as demographic information, self-reported oral health, self-reported dental attendance and history of a bad experience with a previous dentist [42]. Completing the questionnaires will take 10-15 minutes. The interview and questionnaire are completed on the same day. Informed consent and pre-operative data will be collected in the waiting area. The participants undergo VRET at their own pace free of cost. The assessment of state and trait dental anxiety will be done utilizing the VAS-A [32], MDAS [34] and DFS [36]. After T0, the participants will be block randomized as mentioned in Fig. 1 into VRET intervention and informational pamphlet control groups.

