## Sample size

Since the approach of the study is novel, there is scanty comparable research available to use for a sample size calculation. We used the difference between two independent means’ for sample estimation (independent-samples t-test). In a previous study [46] the response within each subject group was normally distributed with standard deviation (MDAS) 4.22. If the true difference in the experimental and control means (MDAS) is 6, we will need to study 12 experimental subjects and 12 control subjects to be able to reject the null hypothesis that the population means of the experimental and control groups are equal with probability (power) 0.9. The Type I error probability associated with this test of this null hypothesis is 0.05. Since drop-outs are unavoidable when collecting follow-up data, the sample number needs to be adjusted for the estimated drop-out rate. We are estimating a drop-out rate of 15 % in this study. Adjusting the sample for 15 % drop-out and 10 % for VR crash results in sample of 30 participants (15 experimental and 15 control participants).

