## Data analysis

The analyses will be performed based on the Consolidated Standards of Reporting Trials (CONSORT) statement regarding e-health [47]. An independent biostatistician will carry out the statistical analysis using SPSS 20.0.The recorded data will be labelled so that the biostatistician will not be able to distinguish between the two groups. All data will be analyzed using an intention-to-treat analysis. We will also conduct a per protocol analyses. Descriptive statistics will be calculated, whereas discrete variables will be summarized by frequencies or proportions. Continuous variables will be reported as means and standard deviations or medians and range (depending on the measurement level of the variables). Data will be checked for differences at T0, T1, T2, T3 and T4 between the VRET and informational pamphlet group using independent samples t-test. Between-group changes at post treatment will be calculated by using a 2 (pre-treatment/post-treatment) × 2 (VRET/Informational pamphlet) repeated measures MANOVA. Post hoc comparisons will be applied if clarification of the main effects of the MANOVA is needed. Effect sizes between the groups will be calculated with Hedges’ g. Clinical significance change analyses as described by Jacobson and Truax [48] will be conducted to determine whether the changes from pre-test to post-test are clinically significant [48]. Missing data analysis will be performed and the reason for non-adherence will be registered.

The continuous monitoring of HR data will help us determine whether the physiological changes diminish following multiple exposures with each scenario (suggestive of habituation-Reliability of therapy).

To evaluate the correlation between subjective measures of VR experience (presence, realism, nausea) with objective measure of HR during each VR scenario, only the first exposure measures will be considered to eliminate the order effects as shown in Table 2.

Since the baseline physiology levels will vary widely between individuals, we will be determining the percentage change from baseline HR during the first exposure of each VR scenario for analyses rather than considering the absolute values. The percentage change of heart rate (%HR) will be calculated as follows:$$ \%\mathrm{H}\mathrm{R} = \left(\mathrm{MeanVR} - \mathrm{MeanBaseline}\right)/\mathrm{MeanBaseline}, \times 100 $$where,

MeanVR: Mean of HR during the VRET of 1^st^ exposure of each VR scenario, and

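### The 1-week, 3-month and 6-month comparisons are unadjusted t-tests although T0 scores are collected before randomisation; adjusting for T0 is a near-free gain in precision, not the repair of an invalid test

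*Protocol article*

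**What the plan says.** The primary objective (Background) is efficacy "in terms of dental trait and state anxiety reductions at 1 week, 3 months and 6 months follow-up among a sample of patients".

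Table 1 shows VAS-A, MDAS and DFS collected in both arms at T0, at T1 and at each follow-up. The Procedure section places T0 ahead of allocation: "After T0, the participants will be block randomized".

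The Data analysis section gives two between-group analyses of these scores:

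- "Data will be checked for differences at T0, T1, T2, T3 and T4 between the VRET and informational pamphlet group using independent samples t-test". No covariate is named.
- "Between-group changes at post treatment will be calculated by using a 2 (pre-treatment/post-treatment) × 2 (VRET/Informational pamphlet) repeated measures MANOVA". This has two time levels and is described for post treatment. The section does not say whether the pre-treatment score is T0 or the T1 preoperative score.

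The clinical-significance analysis runs from pre-test to post-test. The percentage change from baseline applies only to heart rate in the VRET session. The Sample size section assumes the same unadjusted test: "We used the difference between two independent means’ for sample estimation (independent-samples t-test").

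**The concern.** A score on the same scale, taken before randomisation, is usually the best available predictor of the follow-up score. Here it exists for all three anxiety scales, but at T2 to T4 it is not used. Its one use in the t-test sequence is a between-arm test at T0. After proper randomisation that test can detect only chance, and a non-significant result does not show that the arms started level.

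At stake are wider intervals than the data allow in a trial of 15 per arm, and a follow-up difference that carries part of whatever T0 difference chance produced. Fixing the adjustment in advance would also remove any discretion to adjust, or not, after seeing the T0 scores.

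**Working it through.** **Inputs from the protocol.** MDAS SD 4.22, difference 6, type I error 0.05, power 0.9, 12 evaluable and 15 randomised per arm (Sample size); MDAS of at least 15 at screening (Participants); MDAS range 5 to 25 (Primary outcome measures).

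**Assumption.** The correlation r between T0 and follow-up is not given. I use 0.3, 0.5 and 0.7, with 0 as the worst case shown.

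**1. The plan's own figure.** The standardised difference is 6/4.22 = 1.42. A two-sided t-test (noncentral t) has power 0.887 at 11 per arm and 0.914 at 12, so the stated 12 per arm reproduces.

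**2. Unadjusted interval at 12 per arm.** SE = 4.22 × √(2/12) = 1.72. Half-width = t(0.975; 22 df) × SE = 2.074 × 1.723 = 3.57 points.

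**3. Interval adjusted for T0.** SE = 1.723 × √(1 − r²) × √(1 + 1/(2n − 4)), on 2n − 3 = 21 df. The last factor, √1.05, is the price of estimating the slope. At r = 0 the half-width is 2.080 × 1.723 × 1.0247 = 3.67, and it then scales with √(1 − r²).

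| r | Residual variance ratio | Half-width | Power, 6 points | Power, 5 points |
|---|---|---|---|---|
| unadjusted | 1.00 | 3.57 | 0.914 | 0.79 |
| 0 | 1.00 | 3.67 | 0.900 | 0.77 |
| 0.3 | 0.91 | 3.50 | 0.924 | 0.81 |
| 0.5 | 0.75 | 3.18 | 0.962 | 0.88 |
| 0.7 | 0.51 | 2.62 | 0.995 | 0.97 |

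The 5-point difference is an assumed smaller effect. The SEs break even at r of about 0.22 with 12 per arm and 0.19 with 15.

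**4. Would the pre/post MANOVA do the same job if it were run at each follow-up?** Its group-by-time term compares change scores. With equal SDs at both times, the variance relative to the raw-score t-test is 2(1 − r) = 1.4, 1.0 or 0.6 at r = 0.3, 0.5 or 0.7, against 0.91, 0.75 or 0.51 with T0 as covariate. Power for 6 points at 12 per arm would be 0.803, 0.914 or 0.990. That is lower than with adjustment at every r shown, and lower than the plain t-test when r is below 0.5.

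**5. Chance imbalance at T0.** The 4.22 is a within-group SD from a previous study: "the response within each subject group was normally distributed with standard deviation (MDAS) 4.22". It does not suit T0 in this trial, where entry requires MDAS of at least 15 on a scale ending at 25. If T0 scores were spread evenly over the integers 15 to 25 (an assumption), their SD would be √((11² − 1)/12) = 3.16. At 15 per arm the T0 difference then has SD 3.16 × √(2/15) = 1.15. It exceeds 2 points in about 8% of trials and 3 points in about 0.9%. The smallest significant T0 difference is 2.048 × 1.155 = 2.36 points, so a 2-point imbalance would pass the T0 test unnoticed.

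**6. What imbalance does to the estimate.** The shift carried into follow-up is the slope, r × (follow-up SD / T0 SD), times the imbalance. For a one-SD imbalance the T0 SD cancels, leaving r × 4.22 × √(2/15) = r × 1.54, which is 0.46, 0.77 or 1.08 MDAS points at r = 0.3, 0.5 or 0.7. This takes 4.22 as the follow-up SD.

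**The case against.** The strongest reply is that nothing here is wrong. The unadjusted t-test is unbiased over randomisation, holds its 5% error, and is the test on which the sample size rests. That stands.

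A reader might infer that T0 imbalance inflates the false-positive rate. In simulated null trials of 12 per arm with SD 4.22, the rate among trials with a T0 difference above 2 points is about 7%, 10% or 14% at r = 0.3, 0.5 or 0.7. But those trials, about a quarter of the total, are picked out for their imbalance. In the rest the rate is 4.4%, 3.3% or 2.0%, and overall it is 5%. The unconditional interval already allows for this variation.

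A reader might also put 4.22 into the T0 comparison and conclude that imbalances above 2 points arise in 19% of trials and above 3 points in 5%. The entry rule and the scale maximum do not support those frequencies.

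The benefit depends on a correlation that the protocol does not give, and the restricted range of T0 scores may lower it. That stands too, and at 0.3 the gain is only about 2% in half-width.

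Finally, post treatment could be read to include the follow-up visits, so a reader should not take it as stated that the MANOVA stops short of T2 to T4. Two time levels, with T2 to T4 named separately for the t-tests, make that the more natural reading, but it is not explicit. The point does not depend on it, because a change-score comparison is not covariate adjustment. Nor is it a mere omission that a fuller analysis plan would fill: the protocol names a specific test for these visits.

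**Conclusion.** The point holds as a cheap improvement. The protocol leaves avoidable imprecision and uncorrected chance imbalance in the T2, T3 and T4 comparisons, and spends T0 on a test that says nothing useful after randomisation. It is not an invalid analysis, and the trial is not underpowered on its own inputs.

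The size ranges from a 2% narrower interval at an assumed correlation of 0.3 to 27% narrower at 0.7 (1 − 2.62/3.57). This rests on a follow-up MDAS SD of 4.22, 12 evaluable per arm and a linear relation with T0. The MDAS figures do not carry over to DFS or VAS-A, for which the protocol gives no SD, but the variance ratios apply to any scale with the same correlation.

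**What to change.** In the Data analysis section, replace the between-group t-tests at T2, T3 and T4 with a linear model of the visit score on arm plus the T0 score of the same scale. Report the adjusted mean difference with its 95% CI. Use T0 as the covariate, because it precedes randomisation and the T1 preoperative score does not. Present T0 by arm descriptively and drop the significance test there.

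The cost is a sentence or two of text and one degree of freedom. No new data, visits or participants are needed. If the correlation is near zero, the interval widens by about 3% (3.67 against 3.57), and power for 6 points at 12 per arm is 0.900 instead of 0.914.

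### Intention-to-treat is promised, but the only between-group tests named for T2 to T4 are unadjusted t-tests on the scores observed at each visit, and the sample size counts VR crashes as lost participants

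*Protocol article*

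**What the plan says.** The Data analysis section sets the population: "All data will be analyzed using an intention-to-treat analysis". A per-protocol analysis is to be done as well.

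The same section names two between-group analyses of the anxiety scores:

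- Visit-wise tests: "Data will be checked for differences at T0, T1, T2, T3 and T4 between the VRET and informational pamphlet group using independent samples t-test".
- A pre/post by group repeated-measures MANOVA, introduced as "Between-group changes at post treatment will be calculated by using a 2 (pre-treatment/post-treatment" and completed by the two arms as the second factor.

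On missing scores it says only: "Missing data analysis will be performed and the reason for non-adherence will be registered".

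The Sample size section expects loss: "Since drop-outs are unavoidable when collecting follow-up data, the sample number needs to be adjusted for the estimated drop-out rate". It puts a figure on it, "We are estimating a drop-out rate of 15 % in this study", and then adds a second allowance: "Adjusting the sample for 15 % drop-out and 10 % for VR crash results in sample of 30 participants".

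The Background section places the primary objective at 1 week, 3 months and 6 months. Table 1 shows that the T2, T3 and T4 questionnaires go out by e-mail.

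**The concern.** The population that is promised and the tests that are named do not fit together at the visits that carry the primary objective. A t-test at T3, run as named, uses whoever returned a T3 questionnaire. Someone who answered at T0, T1 and T2 but not at T3 contributes nothing to it, and the T0 score plays no part for anyone. The set analysed can change from visit to visit, yet each result would carry the intention-to-treat label.

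The sample-size allowance raises a second difficulty. It counts a VR crash as a lost participant. Under intention-to-treat, a person whose session crashed stays in the VRET arm, and nothing about a crash prevents an answer to an e-mailed questionnaire.

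What is at stake is mainly bias. Higher MDAS scores are worse. If VRET participants who did badly are the ones who stop answering, the observed VRET mean is too low and VRET looks better than it is.

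**Working it through.** **Inputs (Sample size section).** MDAS standard deviation 4.22 ("the response within each subject group was normally distributed with standard deviation (MDAS) 4.22"), true difference 6, power 0.9, type I error 0.05 (two-sided assumed, as the side is not stated), 12 analysed per arm, allowances of 15% and 10%, 15 randomised per arm.

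**1. The plan's own figure.** The exact two-sample t-test (noncentral t) has power 0.887 at 11 per arm and 0.914 at 12, so 12 per arm reproduces. The inflation reproduces as 12 × (1 + 0.15 + 0.10) = 15 per arm, 30 in total. The target is therefore 12 per arm left to analyse after losses, with crashes counted among the losses.

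**2. Planned loss by arm.** The article applies both allowances to both arms, but a VR crash can occur only in VRET.

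- Pamphlet: 15%, leaving 15 × 0.85 = 12.75.
- VRET, allowances added: 25%, leaving 15 × 0.75 = 11.25.
- VRET, allowances compounded: 1 − 0.85 × 0.90 = 23.5%, leaving 15 × 0.765 = 11.5.

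**3. Power.** It is 0.964 with 15 v 15, 0.901 with 11 v 12, 0.925 with 12 v 13, and 0.887 with 11 v 11. Loss on this scale costs little power.

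**4. Bias, moderate case.** Assumptions, not in the documents: a fraction q of the VRET arm is missing, those missing would score g MDAS points worse than those observed, and pamphlet loss is unrelated to outcome. The full-arm mean is then the observed mean plus q × g, so the arm difference is overstated by q × g.

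| VRET loss q | g = 2 | g = 4 | g = 6 |
|---|---|---|---|
| 15% | 0.3 | 0.6 | 0.9 |
| 23.5% | 0.47 | 0.94 | 1.41 |
| 25% | 0.5 | 1.0 | 1.5 |

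**5. Bias, extreme bound.** If exactly the worst-scoring fraction q of a normal sample is lost, the observed mean shifts by SD × φ(z₁₋q)/(1 − q).

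- q = 0.15: 0.274 × 4.22 = 1.16 points, and 1.16/6 = 19% of the planned difference.
- q = 0.25: 0.424 × 4.22 = 1.79 points, and 1.79/6 = 30% of the planned difference.

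**6. Which analyses are exposed.** Table 1 has a preoperative and a postoperative interview, both at T1. If the MANOVA's post-treatment score is that same-day score, drop-out during follow-up hardly touches it. The visit-wise t-tests are then the only named between-group tests that cover T2, T3 and T4.

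**The case against.** A reader might infer that the article makes the main analysis complete-case. It does not say so. T-tests and MANOVA can be run on imputed data, a missing-data analysis is promised without a method, and a fuller plan may supply one. Visit-wise t-tests are also available-case at each visit rather than complete-case across visits. An unnamed imputation method alone would be no finding in a condensed article. This part of the objection stands, so the point rests on the tests that are named and on the treatment of crashes.

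A reader might also infer that the MANOVA loses everyone who drops out during follow-up, or that the whole trial expects 25% loss. The documents support neither. The MANOVA is pre/post only, and the crash part of the allowance can apply to one arm only.

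Pressing the panic button is not documented as ending participation or stopping questionnaires, so it cannot be counted as loss. The Sample size section also does not say in words that crash participants leave the intention-to-treat set; it only counts them in the attrition allowance.

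The 1.2 and 1.8 point figures are extremes. They need the worst scorers to be exactly the ones who vanish, and the 25% case would require technical crashes to select on MDAS, for which there is no reason. They also describe loss that depends on the unobserved score, which a mixed model does not remove by itself.

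Two things remain. The tests named for T2 to T4 make no use of the T0 score or of the other visits, and counting crashes as losses does not fit the stated population.

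**Conclusion.** The concern holds in this limited form. The article commits to intention-to-treat, but for its primary T2, T3 and T4 comparisons it names only unadjusted t-tests on observed scores, and its sample size counts VR crashes as losses that intention-to-treat would keep. Planned loss is about 15% in the pamphlet arm and 23.5% to 25% in VRET, so it may differ by arm.

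The size of the bias is uncertain. Under the moderate assumptions it is 0.3 to 0.9 MDAS points at 15% VRET loss and 0.5 to 1.5 at 25%, against a planned 6; 1.2 and 1.8 points are outer bounds. These figures rest on assumed differences between missing and observed participants and on pamphlet loss being unrelated to outcome. Power is a minor issue. The change should be made because it is cheap and brings the main result into line with its label; the trial is not invalid without it.

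**What to change.** - **Primary analysis.** Replace the visit-wise t-tests with a likelihood-based mixed model for repeated measures in all randomised participants as allocated, with T0 score, arm, visit and arm × visit, and report the arm contrasts at T2, T3 and T4. T0 is collected before randomisation, so it is a proper baseline covariate.
- **Crash and panic-stop participants.** State that they stay in the VRET arm and are still sent every questionnaire.
- **Sensitivity analysis.** The mixed model assumes missing at random, and a participant with no score after T0 adds nothing to its arm contrasts. Add one conservative analysis, for example with missing VRET scores set to their T0 values.
- **Per-protocol set.** Define it by adherence to the intervention, not by questionnaire completion. Someone who stops VRET early but returns every questionnaire is a completer without being per-protocol.

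The cost is a paragraph of analysis wording, slightly more analysis work, and reliance on model assumptions in a sample of 30. The named software fits mixed models, and no new measures are needed.

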## Discussion

The design of this randomized clinical trial offers pathways to address the efficacy of VRET in the treatment of long term trait dental anxiety. Therefore, we developed (KR, [name] and MB) a VRET device based on exposure therapy models and will be testing the efficacy of this intervention among people with dental phobia immediately after therapy, 1 week, 3 months and 6 months post therapy, and will be comparing with the results of an informational pamphlet intervention.

In recent years VRET has become a viable treatment alternative for in vivo exposure therapy as evidence based treatment for specific phobias with the advantage of allowing patients to face their fears in a controlled and thus safe, environment. Patients may not feel the anticipatory fear of getting hurt as they are aware that the VRET simulation is purely virtual and that these situations can be stopped, paused, restarted as well as repeated, whenever, for as many times as deemed necessary [10]. Accordingly, patients’ acceptance of VRET could be relatively high.

Another important advantage of the application of VRET for dental phobia is that it may not require specialized training and the entire exposure process can be completed by a computer in the safety and privacy of the practitioner’s office [10]. To this end, the study is a feasibility study. If proved successful, the VRET device can be rendered by any dental auxiliaries in a general dental practice which could make it a cost-effective solution. For example, because VR technology has applications in telemedicine, in which diagnosis and treatment can be administered from a distant site [49]. This may make VRET applicable in rural dental clinics, in which the therapist might not be available at long distances and the therapist views on a monitor with which the subject is interacting, and comment appropriately and therapeutically.

The strengths of our study design include randomized group allocation, use of validated standardized assessments and a long term follow-up. A limitation of the present study is the absence of IVET as gold standard control group. Yet, it is hoped that the findings of this study will provide evidence in support of the efficacy of VRET and therefore will be an important step in the treatment of dental phobia in the setting of the dental practice.

